#### Economic outcome measures

In this pilot study, the aims of the economic evaluation component are to plan the economic evaluation that would accompany a phase III RCT, identify sources of data and determine how best to collect these. We will undertake a detailed cost analysis of the intervention; collect resource use data and examine response rates and data quality; use the process evaluation to identify any unanticipated costs to students, schools and NSPCC and to consider ways of maximising responses to economic data collection; identify unit costs for the cost components; and review additional literature to identify any new potential sources of data to model long-term costs and outcomes.

In a phase III RCT, the primary economic evaluation would take the form of a within-trial cost-utility analysis, with health outcomes expressed in terms of quality-adjusted life-years (QALYs). Changes in health-related quality of life would be measured primarily from study participants’ perspectives with a secondary analysis examining teacher outcomes. The Child Health Utility (CHU) 9D measure [81] would be used to assess students’ health-related quality of life and the 12-item Short Form Health Survey (SF-12) would be used for this purpose for teachers [82]. In the pilot RCT, we will assess the measures used for this analysis by collecting data on them at baseline and follow-up. The CHU-9 is a validated age-appropriate measure that was explicitly developed using children’s input and has been suggested to be more appropriate and function better than other generic health utility measures for children and adolescents [83]. In a phase III RCT, student and teacher utility values would be collected at baseline and subsequent follow-up points using the selected measures, which would then be converted into utility scores suitable for calculating QALYs using published algorithms. In addition, a cost consequence analysis would be presented with further outcomes. The time horizon would capture costs and outcomes within the trial. In terms of costs, we would present the base-case cost-effectiveness estimate from a public sector perspective, as recommended by the National Institute for Health and Care Excellence’s public health methods guidance. Given that Project Respect will be delivered by a charity, our costing perspective would also be extended to include the voluntary sector.

### Assessment and follow up

Baseline surveys will be conducted before randomisation with two cohorts of students, one nearing the end of year 8 (aged 12–13 years) and one nearing the end of year 9 (aged 13–14 years). Baseline surveys will collect data on socio-demographic variables, pre-hypothesised outcome variables and potential confounders. Where feasible, surveys will be done at the same time of day in all schools. Students will be given an information sheet about the study at least 1 week prior to data collection and an oral description of the study. Students will have the opportunity to ask questions before deciding whether or not to take part. We will be clear about the topics to be explored and the complete anonymity of questionnaire data. Students will then be invited to assent to participate in data collection. All students will be provided with information about school safeguarding officers, other local safeguarding resources (where relevant), a national helpline and other agencies for students experiencing DRV or other forms of abuse. We will also provide students and their parents/guardians with the contact details for the research team to report any concerns relating to the research. As is conventional with UK trials in secondary schools, including trials of sexual health and violence prevention interventions [73, 74, 84], students’ parents/guardians will also be sent a detailed information sheet at least 1 week prior to data collection. They will be asked to contact the school or research team should they have questions or should they wish for their child not to take part. A sample of the information sheets and consent forms used for the study are provided in Additional file 2.

Given the particularly sensitive nature of DRV, we will pilot the use of tablet-based CASI surveys to maximise student privacy and optimise the quality of the data collected. Students will complete surveys confidentially and anonymously with researchers present to explain data collection and support participants where necessary. Teaching staff will be present but will remain at the front of the classroom, helping to maintain order but unable to read student responses. During optimisation, we will ask students about the acceptability of this approach.

We will survey absent students by leaving paper questionnaires and stamped addressed envelopes with their schools. When we conduct follow-up surveys 16 months post-baseline, with students who are near the beginning of years 10 and 11 (aged 14–15 and 15–16 years, respectively), we will collect self-report data on intervention participation, outcomes and potential mediators. Fieldworkers will be blind to school allocation. Based on past experience [84], in the pilot, we anticipate 95% baseline survey participation and 90% at follow-up. We will also conduct online staff surveys at baseline and 16 months post-baseline for the economic and process evaluations.

### Process evaluation

An integral process evaluation, informed by existing frameworks [85–87], has three purposes: first, to examine intervention feasibility, fidelity, reach and acceptability; second, to assess provision of sexual health services and violence prevention in and around control schools; and third, to explore context and potential mechanisms of action, as well as potential unintended effects, in order to refine the intervention’s theory of change and the intervention methods.

#### Intervention feasibility, fidelity, reach and acceptability

In addition to assessing the ‘progression criteria’ outlined in the study’s research question 1 relating to intervention feasibility and acceptability, we will also examine reach and how it varies by student and school characteristics. Data on these outcomes will be collected via: audio-recording of all NSPCC and school-delivered training (fidelity); logbooks completed by teaching staff delivering all curriculum sessions (feasibility, fidelity, costs); structured observations of a randomly selected session per school of one curriculum lesson (fidelity); student surveys (reach, acceptability); staff survey (reach, acceptability of training and intervention overall); interviews with the NSPCC trainer(s) (feasibility, fidelity); interviews with four staff per intervention school, purposively sampled by seniority and which intervention component(s) they are involved in (acceptability, fidelity); interviews with two parents per intervention school, purposively sampled by age and sex of their child (acceptability); and interviews with eight students per intervention school, purposively sampled by year 9/10, sex and involvement in a student-led campaign as part of the intervention delivery (acceptability).

Fidelity will be assessed quantitatively against tick-box quality metrics. For example, each training and curriculum session will be assessed against session-specific quality metrics relating to the topics covered, the exercises used and opportunities for discussion. After the intervention is fully elaborated, the investigators will finalise the fidelity metrics based on the intervention and will ask the Study Steering Committee (SSC) to approve these prior to their use in the process evaluation.

Trained researchers will conduct interviews in private rooms, guided by semi-structured interview guides. Although the qualitative research will not aim to explore students’ personal experiences of sex, relationships, or DRV, disclosures of abuse may occur. In focus groups, we will instruct participants not to disclose any experiences of abuse during the group discussion since we cannot guarantee that all participants would keep this information confidential. All focus groups will be conducted by researchers who have been trained to steer group discussions away from potential disclosures. We will, however, provide the opportunity for participants to speak with the researcher in private after the focus group if they would like help with any issues they are facing. If disclosures of sexual intercourse before age 13 years or of any other abuse occur during qualitative data collection, the researcher will establish whether the reported abuse meets our criteria for referral. If it does, the researcher will inform the student that she or he must report this to the school safeguarding officer. We have defined categories of harm warranting such responses with the advice of a social worker specialising in child protection and in collaboration with NSPCC (see the ‘Ethical issues’ section, below). We will consult with school safeguarding officers in advance to ensure this process is compatible with school policies.

Interviews will be audio-recorded and transcribed in full. Drawing on May’s theory of implementation [86], qualitative research will assess how implementation is influenced by NSPCC and school staffs’ perceptions as to the intervention’s potential workability and integration within the school system, possession of the required norms and relationships to underpin implementation, shared commitment to enact the complex intervention and continuous contributions that are sustained in time and space.

#### Provision in control schools

We will examine sexual health provision in and around control schools to describe our comparator. Data on this will be collected via staff and student surveys; interviews with two staff members per control school, selected purposively by seniority; and four students per control school, selected purposively by year 9/10 and sex.

#### Context and mechanisms of action

Informed by realist approaches [88, 89], using qualitative methods we will aim to explore potential intervention mechanisms and how these interact with contextual factors to enable outcomes, including mechanisms that might give rise to unintended, potentially harmful consequences. We will also explore how potential mechanisms of action might vary with school context and student characteristics, in order to refine and optimise the intervention’s theory of change and intervention methods. Data on context and mechanisms will be collected via interviews with NSPCC trainers, student and staff surveys and interviews with four staff and eight students per intervention school (purposively sampled as described above). Our quantitative research will pilot mediator analyses, as discussed in the next section.

### Approach to data analysis

In the pilot RCT, our primary analysis will determine whether criteria for progression to a phase III RCT are met. Descriptive statistics on fidelity will draw on audio-recordings of training, logbooks completed by teaching staff and structured observations of curriculum lessons. Acceptability will be assessed through student and staff surveys. Recruitment and response rates will be reported in a flow chart and used to refine our power calculation. Pilot RCT analyses will also assess which of our indicative primary outcomes is sufficiently reliable to use within a phase III RCT, assessing response rates, inter-item reliability (using Cronbach’s and ordinal alphas) and fit (using confirmatory factor analysis). In-line with our approach in a previous pilot trial, we will prioritise completion rates and inter-item reliability when judging between measures [84]. We will set the threshold for acceptable reliability at a Cronbach’s alpha of 0.70 or higher. If both measures perform well on this, we will choose the CADRI-s for use in a phase III RCT since this is the more established measure. If neither performs well, we will not progress to phase III without first identifying and piloting alternative measures.

Although the pilot RCT will be underpowered to determine an ICC and prevalence among the comparator of DRV, it will enable a more qualitative assessment of whether estimates derived from North American studies seem to be appropriate for schools in England.

Data from the process evaluation will be analysed to describe provision of violence prevention and sexual health-related activities in and around study schools, contextual influences on intervention feasibility and acceptability and potential mechanisms of benefits and unintended impacts to refine the intervention’s theory of change. Qualitative data will be subject to thematic content analysis using techniques drawn from grounded theory such as in vivo/axial codes and constant comparison [90]. As well as deriving themes inductively from the data, we will also use realist approaches to evaluation [89] and May’s implementation theory [86] to inform analyses, identifying characteristics of the intervention, providers and settings which promote or hinder implementation or which might interact with intervention mechanisms to enable outcomes. Qualitative research will develop hypotheses which will be tested in exploratory quantitative analyses where data allow.

The economic evaluation feasibility component of the study will pilot measures assessing quality of life and assess the feasibility of methods to be used within a full RCT. We will also pilot the primary intention-to-treat analyses of outcomes which will use repeat cross-sectional data as would be done within a phase III RCT, as well as secondary, moderator and mediator analyses. In a phase III RCT, moderator analysis would be conducted to examine how effects vary by student socioeconomic status, sex and ethnicity and by school IDACI and value-added academic attainment. Mediator analysis would examine whether intervention effects on mediators might explain effects on our primary outcomes using established methods [91]. All such analyses will be underpowered in this pilot RCT but will be piloted to refine methods.

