#### Research questions

Is progression to a phase III RCT justified in terms of pre-specified criteria? These criteria are: randomisation occurs and four or more schools out of six accept randomisation and continue within the study; the intervention is implemented with fidelity in at least three of the four intervention schools; the process evaluation indicates the intervention is acceptable to 70% or more of year 9 and 10 students and staff involved in implementation; CASI surveys of students are acceptable and achieve response rates of at least 80% in four or more schools; and methods for economic evaluation in a phase III RCT are feasible.Which of two existing scales—the Safe Dates (SD) and the short Conflict in Adolescent Dating Relationships Inventory (CADRI-s)—is optimal for assessing DRV victimisation and perpetration as primary outcomes in a phase III RCT, judged in terms of completion, inter-item reliability and fit?What are likely response rates in a phase III RCT?Do the estimates of prevalence and intra-cluster correlation coefficient (ICC) of DRV derived from the literature look similar to those found in the UK so that they may inform a sample size calculation for a phase III RCT?Are secondary outcome and covariate measures reliable and what refinements are suggested?What refinements to the intervention are suggested by the process evaluation?What do qualitative data suggest about how contextual factors might influence implementation, receipt or mechanisms of action?Do qualitative data suggest any potential harms and how might these be reduced?What sexual health and violence-related activities occur in and around control schools?

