The SD measure of dating violence is based on self-reported perpetration and victimisation of psychological abuse and of physical and sexual violence in the previous year. Participants are asked ‘How often has anyone that you have ever been on a date with done the following things to you?’ Response options range 0–3, indicating frequency. Items are summed and then recoded 0–3 indicating overall degree of abuse. Psychological abuse is assessed in terms of 14 acts (Cronbach’s alpha = 0.91 for victimisation and 0.89 for perpetration) [47, 60]. Physical and sexual violence are assessed in terms of 18 acts, of which 6 indicate serious physical violence and 2 indicate forced sexual acts (Cronbach’s alphas for perpetration of moderate physical violence = 0.92, for severe physical violence = 0.89 and for sexual violence = 0.86). For victimisation, Cronbach’s alphas are respectively 0.90, 0.86 and 0.74 [47]. The SD measure is one of the most commonly used in research on adolescent dating violence [61] and correlates with poor mental health and various health risk behaviours including other forms of youth violence and substance use [23, 62, 63]. Reliability has been examined in multiple studies of adolescents, but not in the UK to date. We will add introductory text to clarify our interest in both on- and off-line behaviours. Our primary outcome will examine categorical measures of DRV perpetration and victimisation, while secondary outcomes will examine each subscale.

The CADRI measure comprises 92 items assessing DRV victimisation and perpetration over the past year. Subscales cover emotional abuse, relational abuse, controlling behaviours, physical violence and non-consensual sexual activities. Items are rated on a 4-point scale according to frequency, allowing generation of a binary measure of prevalence or a quantitative measure of frequency created from the summed score divided by the number of items. Research has found that DRV as measured via the CADRI scale is correlated during adolescence with early sexual debut, unsafe sex, violence and suicidal ideation [64]. The CADRI instrument has been used in research with young people in the USA, Canada [65, 66] and Spain [67], but not in the UK to date.

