The use of the CADRI measure within trials is problematic due to its length. A short 10-item version of the CADRI, the CADRI-s, has been developed and piloted among school-based samples of students in 9th–12th grade and in at-risk samples in Canada. The new measure was found to be slightly less sensitive than the full questionnaire but to have good reliability, fit and convergent validity with the full measure [68]. We plan to further assess this short version. We will modify the scale by adding text clarifying our interest in both on- and off-line behaviours and adding two items from the original CADRI measure to assess experience of controlling behaviours. The developers of the SD and CADRI-s have permitted our use and modification of these measures. We propose to use the pilot RCT to refine the two existing measures, cognitively test these to inform further refinements and then pilot the measures and assess completion rates, inter-item reliability (using Cronbach’s and ordinal alphas) and fit (using confirmatory factor analysis).

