Informed by the intervention’s theory of change, we will also examine the following mediators (to be assessed for reliability in this pilot trial):Social norms and gender stereotyping. We will use a modified version of a multi-item subscale developed by Foshee [23] measuring acceptance of prescribed norms (acceptance of dating violence under certain circumstances) using a 4-point Likert scale format, and adapt these items to measure injunctive norms (beliefs about others’ attitudes towards dating violence). Items are averaged to create a composite score [23]. We will use a modified version of items used by Cook-Craig et al. to measure descriptive norms (beliefs about whether DRV is common) [76]. We will measure gender stereotyping using a modified version of the 16-item Attitudes Towards Women Scale, which has high reliability and uses a 4-point Likert scale format [77]. We will adapt these items to measure injunctive norms (beliefs about others’ attitudes towards gender stereotypes).Self-reported awareness of services, and help seeking for victims and perpetrators. We will assess these via existing single-item self-report measures [23].Communication and anger management. We will assess these using the Modified Sexual Communication Survey (MSCS) and SDQ respectively. MSCS measures open sexual communication with a current or potential partner [78]. The scale includes 21 eight-point Likert scale items examining frequency and has excellent reliability [79, 80].Dating violence knowledge. This will be measured using a modified version of a reliable multi-item scale involving true/false questions on help-seeking and definitions [40].Downloading and use of the ‘Circle of 6’ app will be measured by a new single-item measure.

To ensure student surveys are age-appropriate, items with sensitive sexual content will be excluded at baseline but included at 16-month follow-up.

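### When both scales reach alpha 0.70 the CADRI-s is taken by default, so fit, and a difference in completion, cannot decide the phase III outcome measure, and the reason given is not supported

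*Protocol article*

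**What the plan says.** Research question 2 (Methods, Research questions) asks which of SD and CADRI-s is better for victimisation and perpetration in phase III, "judged in terms of completion, inter-item reliability and fit". The Outcome measures section names the same three criteria and says there is no clear evidence favouring either scale.

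Approach to data analysis turns this into a rule:

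- Priority: "we will prioritise completion rates and inter-item reliability when judging between measures".
- Standard: "We will set the threshold for acceptable reliability at a Cronbach’s alpha of 0.70 or higher".
- Both scales pass: "we will choose the CADRI-s for use in a phase III RCT since this is the more established measure".
- Neither passes: no progression until other measures have been found and piloted.

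The case in which only one scale passes is not written out.

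On the standing of the two scales, Outcome measures says of SD: "The SD measure is one of the most commonly used in research on adolescent dating violence". It adds that SD's reliability has been studied several times in adolescents, though not in the UK. Of the CADRI-s it says: "The new measure was found to be slightly less sensitive than the full questionnaire". The same sentence credits the CADRI-s with sound reliability, fit and agreement with its parent scale. The CADRI-s has 10 items, was piloted in Canada, and gains two further items in this study.

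**The concern.** Choosing the scale is one of the pilot's headline outputs, because it fixes the instrument for both phase III primary outcomes. A head-to-head comparison is useful only if its results can change the choice. Here the plan collects data on three criteria, then names the winner in advance for the case where both scales are adequately reliable. The pilot could find SD better completed and better fitting and still carry the CADRI-s forward.

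The default would be less troubling if its reason held, since a pre-specified tie-break is legitimate. But the reason is a claim about which scale is better established, and the article's own description of the two scales points the other way.

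**Working it through.** The plan gives no figure to reproduce. The check follows the rule through its branches, asks which branch is likely, and sets the reason beside the article's description of the scales.

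**1. The rule by branch.** Each alpha either reaches 0.70 or does not. Completion may favour either scale, and so may fit, giving 2 × 2 = 4 combinations within each alpha result. The rows where only one scale passes assume that the passing scale is taken, because the article does not say.

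| Alpha of 0.70 or higher | SD better on both | SD completion, CADRI-s fit | CADRI-s completion, SD fit | CADRI-s better on both |
|---|---|---|---|---|
| Both | CADRI-s | CADRI-s | CADRI-s | CADRI-s |
| CADRI-s only (assumed) | CADRI-s | CADRI-s | CADRI-s | CADRI-s |
| SD only (assumed) | SD | SD | SD | SD |
| Neither | no progression | no progression | no progression | no progression |

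The point rests on the first row, which is written in the article.

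**2. Which branch is likely.** The SD alphas given in Outcome measures are:

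- psychological abuse: 0.91 (victimisation), 0.89 (perpetration);
- perpetration of moderate physical, severe physical and sexual violence: 0.92, 0.89, 0.86;
- victimisation, same order: 0.90, 0.86, 0.74.

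All 8 of 8 exceed 0.70; the lowest clears it by 0.74 − 0.70 = 0.04. No alpha is quoted for the CADRI-s, but its reliability is called good. The first row is therefore the one that the article's evidence points to.

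**3. What the condition covers.** The words 'on this' follow directly after the alpha threshold, so the plain reading is alpha alone. A wider reading takes in completion, because completion is prioritised a little earlier in the same paragraph.

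- Plain reading: once both alphas pass, neither completion nor fit can change the choice.
- Wider reading: a scale with poor completion might not count as performing well. But no completion standard for a scale is stated. The 80% figure in the progression criteria concerns survey response by school, and both scales sit in the same survey. Two scales with acceptable but different completion would both perform well, and the CADRI-s would still be taken.
- On either reading, fit has no role once both scales pass.

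This conflicts with research question 2, which lists fit, and with the statement in the same paragraph that completion has priority in judging between the scales.

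**4. The reason against the description.**

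| | SD | CADRI-s |
|---|---|---|
| Use | among the most used in the field | short form piloted in Canadian samples |
| Reliability evidence | several adolescent studies | the development and pilot work |
| Changes here | adapted, with introductory text added | adapted, with text and two items added (10 + 2 = 12) |
| UK evidence cited | none | none |

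The wider use cited in the USA, Canada and Spain belongs to the full 92-item CADRI, which the article sets aside for trials because of its length.

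**The case against.** The strongest defence is that a pre-specified tie-break between two adequate scales is good practice, and that the article openly ranks completion and reliability above fit. The CADRI-s also inherits some standing from its parent, has favourable psychometric results and is shorter. Both scales are being adapted, so neither enters the pilot in its established form. Nothing in the both-pass branch alters a progression criterion, a sample size or participant safety.

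Much of this stands. A tie-break is legitimate, and the CADRI-s may prove the better choice. But a tie-break should apply after the stated criteria have failed to separate the scales; this one applies as soon as both reach 0.70. Ranking fit lower does not explain giving it no role. The parent's standing does not carry over to a short form that the article itself calls new.

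Some stronger readings are tempting but not supported:

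- *SD is certain to pass, so everything hangs on the CADRI-s alpha.* The quoted alphas come from earlier work with the unadapted scale, and none is from the UK. The lowest, 0.74, leaves little room.
- *Completion is irrelevant.* That holds only on the plain reading of the condition.
- *The CADRI-s is less sensitive than SD.* The article compares it only with the full CADRI.
- *The 0.70 bar favours one scale because alpha rises with item count.* The relation is r = α / (k − (k − 1)α), where r is the mean inter-item correlation needed. At α = 0.70 it gives 0.068 for 32 items and 0.163 for 12. But SD alphas are reported by subscale: 14 items need 0.143, 6 need 0.28, and a two-item sexual subscale would need 0.7/1.3 = 0.54. The direction depends on how alpha is computed. A stricter bar for the shorter scale would in any case count against the CADRI-s, the scale the default favours.
- *Baseline alphas would mislead.* The article says that "items with sensitive sexual content will be excluded at baseline but included at 16-month follow-up", but not which violence items this removes. The choice of survey wave is commonly left to an analysis plan.

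**Conclusion.** The point holds for the branch in which both scales reach 0.70. There the CADRI-s is chosen in 4 of 4 combinations of completion and fit. Fit cannot affect the choice on any reading. Completion cannot on the plain reading, and on the wider one a difference between two acceptable scales still does not decide. The branch is likely on the article's figures but not assured. The reason given for the default is not supported by the article's own account of the two scales.

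This should be corrected, but it does not threaten the pilot. It weakens the answer to research question 2 and leaves the listed progression criteria untouched. The conclusion assumes that the rule will be applied as written. The assumption about the case where only one scale passes does not affect it.

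**What to change.** Remove the CADRI-s default and its reason. State instead that when both scales reach 0.70, the choice is made in this order:

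1. completion;
2. reliability and confirmatory factor fit, as comparative criteria;
3. if these do not separate the scales, the shorter scale, on grounds of respondent burden.

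The third step has support in the article, which already treats length as a problem in trials. It may well lead to the CADRI-s, but for a stated and defensible reason. Say that the comparison uses follow-up data with the full item set, and write out what happens if only one scale passes.

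The cost is a few sentences, with no extra participants or data collection. The wording should be settled before any comparison of the scales is examined. Randomising which scale comes first on the tablet is an optional extra. It could apply only to follow-up, since baseline surveys were complete at submission, and would not reach absent students, who use paper forms.
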